#### Interventions

The brief PA counseling (PAC) program will comprise 8 sessions (120 min each), every fifteen days, addressing the following themes: reasons to change, an introduction to the PAC-WOMAN program and principles, types of physical activity and their benefits, strategies on how to become more active and less sedentary, how to safely practice exercise at home, the importance of social support for doing more physical activity, barriers and facilitators for becoming more active, development of coping plans and strategies to overcome those barriers, establishing SMART goals, self-monitoring, medical aspects related to symptom management in breast cancer survivors, body image and self-acceptance, sharing experiences with role models, and re-evaluating action plans.

To increase the potential for long-term behavior change, it is important to target theoretically proposed mechanisms of change and incorporate evidence-based behavior change strategies. Self-Determination Theory (see Rationale for the PAC-WOMAN trial), and several evidence-based behavior change techniques, will be used throughout the intervention. The goal will be to empower participants to develop self-regulation resources, fueled by autonomous motivation to integrate physical activity into daily lives, even in the face of adversity, and thus sustain changes in physical lifestyle. The basic psychological needs of autonomy, competence, and relatedness [28] will be supported in all sessions and intervention materials. More specific SDT-based behavior change strategies will include the provision of choice, meaningful rationale, connection between participants’ health behavior and deep inner values, goal setting, action planning, self-monitoring, coping planning, weighing pros and cons of change in the context of held values and life priorities. Group-based sessions will allow the exchange of experiences, feelings, difficulties, and effective solutions to overcome them, in a respectful, non-judgmental, and supportive environment. The portfolio of strategies, and intervention motivational climate, is in accordance with systematic reviews in this regard [41]. Exercise professionals, previously trained in brief counseling skills for health behavior change and its implementation, will deliver the sessions.

A participants’ manual was developed, including a toolbox supporting each session. An activity tracker will be provided to all participants to facilitate self-monitoring. An Exercise Booklet was also created, including different exercises that can be performed at home, accompanied by QR codes with complementary instructive videos. An invested role model (a women previously diagnosed with breast cancer) will illustrate the exercises in the booklet during one of the sessions to show the easiness of their completion. Participants will be prompt to use the booklet as they see fit, during their daily lives, in an integrated fashion (passible to be integrated in the long term) and at a self-selected pace.

The structured exercise program was designed based on the most recent guidelines for exercise prescription and safe practice in cancer populations [12, 19, 59]. A group-based supervised program comprising 32 sessions (over 4 months), lasting 90 min each, and taking place twice a week, was developed. The program combines mobility, aerobic, and strength exercises, respecting a periodization model of four mesocycles of 8 sessions, with progressive intensity and complexity, following the periodization model for each exercise component. Once every 15 days, a thematic group class will be offered to participants, so that they can explore different physical activities and enhance their exercise experience.

Each session will be organized into four components: (i) warm-up—a 10 to 30-min combination of articular mobility exercises and body weight activities; (ii) muscular strength—30 to 45 min, 6–7 large muscle group exercises with an intensity of 60–80% of one maximal repetition (10–15 repetitions, 2–3 sets); (iii) aerobic training—20 to 30 min of a cardiorespiratory workout modality chosen according to participant’s preferences (treadmill, elliptic, bike and row machine) with an intensity of 40–60% of reserve heart rate; (iv) cool-down (5 min). Group sessions will be provided in a person-centered, positive interpersonal environment, by qualified exercise professionals.

An individualized target zone intensity will be previously determined for each participant, based on a preliminary physical evaluation, and monitored during exercise sessions using perceived exertion scales [60] and heart rate monitors (*Polar Club software*). During the sessions, participants’ potential exercise-related adverse effects will be monitored and registered, as well as individual attendance and intensity zone compliance. If participants present any limitations during the session, the exercise prescription will be adapted to respect their individual needs.

Patients allocated to the control group (i.e., waiting list) are asked to continue their daily routines, receiving their standard medical care. No additional instructions will be given to the control group. At the end of the study, the control group will be offered the structured exercise program for 4 months. This type of control group was chosen to allow us to clearly establish whether the tested interventions are effective and superior to no intervention at all.

#### Intervention facilitators training

PAC intervention facilitators will receive training on motivational counseling skills, congruent with a person-centered, SDT-based approach, by a certified trainer. A detailed intervention manual, to support the delivery of the sessions, was produced. It details all the components of each session, including: a) goals and components for each session; b) the importance of each component (the “why”); 2) tips for implementation (the “how”); 3) time allocated to each component/task; 4) materials needed. Intervention counsellors will complete initial training sessions, performing mock counseling encounters with participants concerning the sessions to be delivered. Furthermore, ongoing supervision will also be provided, via weekly meetings to discuss session implementation challenges, deviations or required adjustments to the manual (planned activities for each session), feedbacks, and challenges from participants’ processes.

The supervised structured exercise program was implemented by certified exercise professionals, with a master’s degree in Exercise and Health, and a recognized Advanced Qualification in Physical Exercise and Cancer (provided by Liga Portuguesa Contra o Cancro). An exercise intervention manual was created to guide the interventionists in the implementation of the program. This manual includes information about 1) safety measures and alert signs and symptoms the interventionists should be aware of, 2) the structure of the mesocycles in terms of exercise doses (volumes, intensities), exercises, and specific goals, 3) planned thematic group classes, 4) required equipment and clothes.

#### Criteria for discontinuing or modifying allocated interventions

This is an adaptive, pragmatic trial, subject to real world conditions, thus adaptations may be needed. Data retrieved during trial implementation (mainly from process evaluations, via focus groups with participants at the end of each cohort and interviews with session facilitators, staff from recruiting hospitals and stakeholders) will help to decide the need to adjust aspects of the study as it continues (without undermining the validity and integrity of the trial) [61]. For instance, adjustments might be made in the order or interval between the sessions, based on participants' feedbacks; group allocation ratios might be adapted if recruitment takes longer than expected and, for timely purposes.

It is important to highlight that the PAC-WOMAN trial comprises two non-invasive interventions, with minimal risk of harm. Participants will go through a comprehensive assessment at baseline and those enrolling in the structured exercise program will be provided with a tailored, individualized, prescription, with a gradual progression, always adapted to their needs and capacities. Participants will be asked to report any adverse event and we will keep a close contact with the medical team, always assuring participants’ safety. Also, a personal accident insurance will be contracted and triggered whenever needed.

#### Strategies to improve adherence to interventions and follow-up assessments

One of the major risks in this study is the low compliance of patients to the interventions and assessments. Although most cancer survivors manifest interest in participating in physical activity [15], their lifestyle and implemented routines may interfere with their participation. In addition, a severe decline in physical function is expected to occur during AI therapy, which could potentially lead to increased dropout rates. Nonetheless, the research team includes medical oncologists, physiatrists, and qualified exercise professionals that will assure a close proximity with participants throughout the course of the intervention, assess their experiences and opinions about the program and ways of improving it, and provide a rationale for all the activities involved in the intervention, making sure they continue committed to the trial’s protocol. Moreover, a qualitative analysis (through focus groups) will be applied to enhance the understanding of the patients’ perspectives about: the impacts of the intervention in their daily life; benefits and disadvantages of participation; functional aspects (e.g., dose, procedures, structure) of the intervention; and suggestions of improvement. To increase adherence to follow-up assessments, a session on healthy nutrition for cancer survivors will be offered at this point, as this is a topic that gets a lot of interest among women. Also, at each assessment timepoint, a treat will be offered to participants to stimulate their adherence to the evaluations (e.g., using the gym pool for the day of assessments; a week voucher to try out different gyms), scheduled at a time of their convenience. Participants will also receive an early reminder of the approaching assessment point, and then gentle reminders confirming the date, time, and location of their upcoming visit on the day before.

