#### Assessments

Participants will be assessed at four time points: baseline (T_0_), 4 months (intervention’s end; T_1_), and 10 and 16 months (T_2-_T_3_; during follow-up). A schematic description of all the measurements by timepoint is presented in Table 2. Assessments will take place in standardized conditions, at the exercise setting, in a calm comfortable environment, in small groups, with a group of study technicians attending every assessment period. At each assessment point, the research staff provides participants with an accelerometer, which they are required to wear for a week, and schedules an evaluation visit to the exercise setting, where participants complete the full battery of assessments, described below, and according to the assessment plan for that timepoint. An individual report with the assessment results will be provided to each participant at the end of each assessment period is complete. Participants will be contacted close to each assessment point to determine any changes in their contact or personal information that may have occurred, especially in the fulfillment of the eligibility criteria.

**Table 2 Tab2:** Measurements’ timeline

	**Intervention**		**Follow-up**	
	**T0 Baseline**	**T1 4 months**	**T2 10 months**	**T3 16 months**

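### Attendance treats are exercise access, are not limited by arm and are not kept out of the accelerometer week, which fits poorly with a no-intervention control

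*Protocol article*

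**What the plan says.** The section on strategies to improve adherence states that "at each assessment timepoint, a treat will be offered to participants to stimulate their adherence to the evaluations". The two examples are "e.g., using the gym pool for the day of assessments; a week voucher to try out different gyms". The same section adds: "To increase adherence to follow-up assessments, a session on healthy nutrition for cancer survivors will be offered at this point". Neither offer is restricted to an arm, and the article does not say which visit the nutrition session belongs to.

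Under Interventions, controls are asked to keep to their usual routines with standard care and receive no further instructions. The stated reason for this control is "to clearly establish whether the tested interventions are effective and superior to no intervention at all". The cost-effectiveness paragraph under Statistical methods also uses a no-intervention arm as comparator.

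Under Assessments, visits take place at baseline (T0), 4 months (T1), 10 months (T2) and 16 months (T3), and at each of them "the research staff provides participants with an accelerometer, which they are required to wear for a week, and schedules an evaluation visit". Primary outcomes specifies continuous wear for 7 days and nights. It also lists the Activity Choice Index, which looks back over the past month.

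**The concern.** Physical activity is a primary outcome. A pool session or a week of free gym entry is a small prompt towards that behaviour, offered by the trial itself, to controls as well as to the intervention arms. Two things are at stake.

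- **Measurement.** If a treat is used during the wear week, activity prompted by the trial is recorded as habitual activity. With last observation carried forward, such a value could also stand in for later missing visits.
- **Contrasts.** The arms may not respond alike. A gym voucher may be an inactive control's first contact with a gym. For women in the structured exercise arm it continues the setting of their 32 sessions. Women in the counseling arm were taught free-living activity. A difference in response would enter the comparisons with control and the counseling-versus-exercise comparison, which is itself a primary aim.

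The nutrition session raises a separate and smaller matter. The section on potential covariates treats diet as unrelated to the interventions but able to affect body composition, a secondary outcome. The trial nevertheless offers diet education of its own.

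**Working it through.** The protocol states no figure for this point, so the check sets the sections side by side and adds illustrations on stated assumptions.

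**Step 1: who is exposed, and when.** The treats go to participants at each assessment, and all participants are assessed at T0, T1, T2 and T3. Randomization and blinding places allocation after baseline assessment is complete. A treat used on the T0 assessment day is therefore pre-allocation and balanced in expectation. Exposure that can differ by arm comes from treats at T1, T2 and T3, and from a T0 voucher redeemed after allocation.

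**Step 2: timing against the accelerometer.** The article says "At each assessment point, the research staff provides participants with an accelerometer, which they are required to wear for a week" and that a visit is scheduled. Two orders are compatible with this:

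- Wear week before the visit: a treat handed over at the visit falls largely outside the recording.
- Wear week starting at the visit: pool use that day and a voucher used that week fall inside it.

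The article fixes neither order, so overlap is possible and not shown.

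**Step 3: effect on a between-arm difference.** Let D be the true difference in SD units, and let r_I and r_C be the shifts in recorded activity caused by treats in the intervention and control arms. The expected observed difference is D + (r_I − r_C). No value of r is given. Assume D = 0.30:

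| Response to treats | Observed difference | Change |
|---|---|---|
| Equal in both arms | 0.30 | none |
| Controls respond more by 0.05 | 0.25 | −0.05/0.30 = −17% |
| Controls respond more by 0.10 | 0.20 | −0.10/0.30 = −33% |
| Intervention arm responds more by 0.05 | 0.35 | +17% |
| Intervention arm responds more by 0.10 | 0.40 | +33% |

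The same expression applies to structured exercise versus counseling, with those two arms' shifts in place of r_I and r_C.

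**Step 4: what dilution would do to power.** Assume 1:1:1 allocation, the protocol's 25% dropout and a standardised difference of 0.5. Then 122 × 0.75 = 91.5, or 30.5 per arm. Two-sided power at 0.05 is approximately Φ(δ√(n/2) − 1.96), with √(30.5/2) = 3.905.

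| Share of difference removed | δ | Power |
|---|---|---|
| 0% (also the equal-response case) | 0.50 | 0.50 |
| 10% | 0.45 | 0.42 |
| 20% | 0.40 | 0.35 |
| 30% | 0.35 | 0.28 |
| 50% | 0.25 | 0.16 |

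**Step 5: effect on the recorded level.** Assume two reward sessions of 45 minutes inside the wear week: 2 × 45 = 90 minutes added to that week. This inflates the level in any arm where it happens. It affects a contrast only if arms differ.

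**Step 6: carry-over to the next visit.** Visits are 4, 6 and 6 months apart, while the measures cover 7 days or the past month. For a treat used soon after one visit to reach the next measurement, it would have to change habits for months. Nothing in the article supports that. Overlap at the same visit is the more credible route.

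**The case against.** The treats are small and are given only as examples. Their timing relative to device return is the sort of detail that a condensed article leaves to the full protocol or a manual. Low compliance with assessments is named as a major risk, so incentives serve validity too. An equal response cancels, and the plausible unequal responses pull in opposite directions: stronger uptake by controls shrinks the structured-exercise contrast, and stronger uptake in the exercise arm enlarges it. Controls' activity is measured at every visit and food intake at T0, T1 and T3, so some change would be visible.

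Most of this stands, and it rules out three stronger readings that a reader might infer.

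- **That the control arm is in effect treated.** A pool day, a voucher week and a nutrition session are a minor co-intervention beside 32 supervised sessions or 8 counseling sessions. The wording about no intervention is naturally read against those programmes. Inclusion of controls is the natural reading of an offer to participants, but it is not stated outright.
- **That the treat acts on activity while it is being measured.** The article leaves the order open.
- **That effects are diluted by 17% to 33%.** That requires controls to respond more than the intervention arms, by an assumed amount.

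The nutrition session cannot carry the activity argument either, because nothing links it to measured activity. What the objection does not remove is that both chosen examples act on the behaviour being measured, are open to all arms as written, and are not separated from the measurement week.

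**Conclusion.** The point holds as an avoidable risk of contamination. The treats named are exercise access, are not limited by arm, and are not kept outside the 7-day recording issued at the same assessments. This sits poorly with a comparator meant to represent no intervention.

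Recorded activity can be inflated, and contrasts can be distorted if arms respond differently. Neither the size nor the direction can be derived from the article: the SD-scale and power figures rest on assumed differences of 0.30 and 0.5 SD and assumed responses, and the 90 minutes on an assumed number and length of sessions. Bias has not been shown, and under an equal response there is none in the contrasts. The case for change is that the remedy is cheap and a primary outcome is involved.

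**What to change.** In the section on adherence strategies:

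1. For the remaining assessments before T3, replace pool and gym treats with rewards of similar value unrelated to activity or diet. At minimum, hand over any such treat only after that visit's accelerometer has been returned and its questionnaires completed.
2. Offer gym access and the nutrition session after the T3 visit and T3 wear week.
3. State which arms are offered the treats.
4. For treats already given, record and report receipt by arm and visit.

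The cost is a slightly less attractive or later incentive, which matters somewhat given the planned 25% dropout. There would also be some difference between earlier and later cohorts: by 27 April 2023, 68 of the 122 women had been randomized. Releasing the same treats after measurement keeps the incentive and protects that visit's recording. It does not exclude an effect on activity between visits, so item 4 is needed either way.

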#### Assessments

Participants will be assessed at four time points: baseline (T_0_), 4 months (intervention’s end; T_1_), and 10 and 16 months (T_2-_T_3_; during follow-up). A schematic description of all the measurements by timepoint is presented in Table 2. Assessments will take place in standardized conditions, at the exercise setting, in a calm comfortable environment, in small groups, with a group of study technicians attending every assessment period. At each assessment point, the research staff provides participants with an accelerometer, which they are required to wear for a week, and schedules an evaluation visit to the exercise setting, where participants complete the full battery of assessments, described below, and according to the assessment plan for that timepoint. An individual report with the assessment results will be provided to each participant at the end of each assessment period is complete. Participants will be contacted close to each assessment point to determine any changes in their contact or personal information that may have occurred, especially in the fulfillment of the eligibility criteria.

**Table 2 Tab2:** Measurements’ timeline

	**Intervention**		**Follow-up**	
	**T0 Baseline**	**T1 4 months**	**T2 10 months**	**T3 16 months**
**Primary outcomes**				
Physical activity/sedentary behavior (objective and self-reported)	X	X	X	X
Lifestyle physically active choices	X	X	X	X
Quality of Life	X	X	X	X
Healthcare use	-	X ^a^	-	-
**Secondary outcomes – Physical Measures**				
Body composition	X	X	X	X
Cardiorespiratory fitness	X	X	X	X
Muscular strength	X	X	X	X
Upper limbs flexibility	X	X	X	X
Physical function	X	X	X	X
Adverse events	X	X	X	X
**Secondary outcomes—Psychosocial Measures**				
Perceived intervention climate	-	X	-	-
Exercise motivational regulations	X	X	X	X
Exercise needs satisfaction/frustration in exercise	X	X	X	X
Affective response to exercise	X	X	X	X
Exercise self-efficacy	X	X	X	X
Self-regulation skills	**-**	X	X	X
Subjective Pain	X	X	X	X
Sleep quality	X	X	X	X
Body image	X	X	X	X
Depressive symptoms	X	X	X	X
Psychological well-being	X	X	X	X
